### Outcome

The outcome for the prediction model is an individual’s absolute risk of poor outcome (chronic pain and disability) at 6 months postinjury. Outcome will be measured using the Chronic Pain Grade Scale (CPGS),^21^ which combines pain intensity and pain-related disability over the preceding 6 months into a single measure of pain *severity*. The CPGS has previously been used to assess the severity of body-wide chronic pain in general population,^22^ primary care^23^ and post-trauma^24^ populations. Each item of the CPGS relates to at least one of the three categories of the International Classification of Functioning, Disability and Health (ICF)^25^: impairment, activity limitations and restricted participation. Furthermore, all ICF categories are encompassed by the CPGS.^26^ The CPGS is a unidimensional scale, with good internal consistency across different pain populations; Cronbach’s alpha of 0.84 to 0.91 in back pain, 0.79 for headache and 0.84 for temporomandibular pain.^21 27^ With regards to construct validity, cross-sectional and longitudinal studies of general practice patients have shown high scores on the CPGS, indicating greater chronic pain, to be associated with higher rates of unemployment, greater pain impact scale scores, greater use of opioid analgesics and physician visits, depressed mood and lower self-rated health status.^21 27 28^ For convergent validity, the CPGS has been found to have good correlation with equivalent dimensions of the SF-36.^27 28^ In terms of responsiveness, changes in score over time in patients with chronic musculoskeletal pain correlated significantly with changes in SF-36 scores.^29^ The CPGS has also been shown to have good test–retest reliability in primary care patients with back pain (weighted kappa 0.81, 95% CI 0.65 to 0.98).^27^

Although pain persistence is not used in assigning pain grade, a measure of pain days in the prior 6 months is included in the CPGS.^30^ The responses on the remaining seven items are used for computing scores for the three subscales of the CPGS^21^: characteristic pain intensity, disability score and disability points. The characteristic pain intensity score (range: 0–100) is obtained by calculating the mean of three pain intensity measurements: ‘at the present time’, the ‘worst pain’ in the preceding 6 months and the ‘average’ pain over the preceding 6 months. The disability score (range: 0–100) is obtained through the mean ratings of how much the pain has interfered in performing activities of daily living, recreational, social and family activities, and work (including housework) activities in the last 6 months. The disability points are scored 0–3 and are derived from a combination of ranked categories of the number of disability days (the number of days that the respondent was away from usual activities in the preceding 6 months due to pain) and disability score. Based on these scores, the participant’s chronic pain and disability status can then be classified into one of the five ordinal categories of chronic pain severity^21^: no pain (Grade 0), low disability and low intensity pain (Grade I), low disability and high intensity pain (Grade II), high disability and moderately limiting intensity pain (Grade III), and high disability and severely limiting intensity pain (Grade IV). As in previous studies, poor outcome will be defined as grade ≥II.^23 31–34^

### Candidate predictors

Candidate predictors have been selected that are: (1) reliable and valid measures of their domain, and (2) have a theoretical association with the development of chronic pain. Both modifiable and non-modifiable candidate predictors are included. Candidate predictors are summarised in table 1, with further detail in the online supplementary file S1. Table 1 details important data that will be measured at 3, 6 and 12 months postinjury to explore the clinical course of recovery following injury in the shorter and longer terms. All data collection will be standardised through protocols and clinical report forms.

10.1136/bmjopen-2017-017876.supp1Supplementary data

### Data handling

Blood samples will be collected through the clinical and research nurse teams, while the participant is in the hospital, and either analysed immediately (C-reactive protein) or securely stored for subsequent analysis (cell-free DNA). Baseline self-reported questionnaires, pain and injury drawings, and physical assessments will be collected by one of three trained assessors from the study team. Inter-rater reliability studies (across two assessors) will first be conducted in both healthy and trauma populations to inform definitive testing protocols. The order of physical assessment data collection will be randomly assigned (using computerised randomisation software) according to the modality of testing and by site, to prevent order effects. Follow-up self-reported questionnaires will be posted to participants at their home addresses; with up to two postal reminders and a telephone call for non-response. All questionnaires will be formatted so that data can be scanned or entered directly into an electronic database. Following data entry, data will be checked by a second researcher for completeness and accuracy. In addition, regular audits of data collection and storage will be performed by an independent study management committee. Participant identifiable information will be securely stored within the hospital, in line with current United Kingdom data protection legislation, and only accessible by the site Principal Investigator and Research Nurse team who will not be involved in data analysis. All outcome measure data will be securely transferred within an anonymised database file to physically secure servers at the University of Birmingham, and stored for a period of 10 years in line with Research Governance procedures. Participants will receive usual care and interventions received will be recorded for descriptive analysis. Anonymised data will be analysed using IBM SPSS Statistics.

### Sample size

In predictive modelling, a larger sample size enables lower bias and variance, and permits the prospective prediction of new observations.^15^ The number of predictors will be reduced using exploratory factor analysis. This process will ensure that the sample size provides at least 10 cases per candidate predictor, to adequately power the final regression analysis.^35 36^ Data will be collected for an estimated 300 participants per cohort (n=600 total) to allow for withdrawals (primarily expected deaths within the first 3 months) and losses to follow-up, so that final data are available for 250 participants per cohort (n=500 total).

### Statistical analysis methods and management of missing data

For each cohort, potentially eligible patients, numbers examined for eligibility, confirmed eligible, recruited into the study, completing follow-up and analysed will be reported in a flow diagram. Reasons for non-participation, exclusion, drop-outs and withdrawal (eg, death) will be reported at each stage. Participant characteristics will be descriptively presented. For each variable of interest, the number of participants with missing data will be reported.

For the first cohort to develop the predictive model, an initial exploratory data analysis stage will summarise the data.^15^ Correlations between candidate predictive factors will be calculated at baseline. Outcome (CPGS) scores will be dichotomised into good and poor categories as described previously. Data reduction will use exploratory factor analysis to assess factor loading of candidate predictors (summary scores) on poor outcome at 6 months. This will enable the number of candidate predictors entered into the final model to be reduced to 25, which can be supported by the cohort sample of 250. This process reduces the risk of over-fitting the model and the risk of selecting the wrong variables due to correlation between predictor variables (multicollinearity).^37^

Statistical modelling for prediction has been planned *a priori*. To explore the influence of each predictive factor on poor outcome at 6 months, a logistic multivariable regression model will be fitted to the dichotomised outcome scores to calculate low and high risk of poor outcome. Odds ratios for each candidate predictive factor will be reported, adjusted for other factors and account for clustering (eg, level of injury severity). If necessary, multiple imputation^38^ will be used to deal with missing outcome data. The characteristics of those patients with and without 6-month data will also be compared, to inform whether patients with no 6-month data were missing at random. Reduced multivariable analyses will be considered if necessary (eg, removing one of two candidate predictive factors that are highly correlated at baseline), to examine the robustness of the conclusions.

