### Risk groups and development of the predictive screening tool

The predictive model will be used to develop a risk stratification tool to inform an individual’s absolute risk of poor outcome. The stratification tool will inform clinical decision-making for precision rehabilitation. Items will be selected for the model if they are statistically significantly (P<0.05) associated with poor outcome in the logistic regression analysis, and those deemed clinically important to retain using expert opinion (regardless of statistical significance, study steering group) to improve face validity for clinicians and avoid overfitting of the model.^37^ The regression model with included predictive factors will be fitted to the data from the first of the two cohorts to obtain a final set of parameter estimates (i.e. alpha and beta terms), which will be used to form the model. An important requirement of the stratification tool is that it should be sufficiently brief to facilitate use in clinical practice. Thus, we will look to simplify the model where possible to facilitate its use, but without important reduction in its predictive ability in terms of calibration and discrimination. For example, if multi-item questionnaire scores are included in the model, then we will evaluate whether just one of the questionnaire items is sufficient. Ideally, this process will result in a full and simplified model.

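### Exploratory factor analysis cannot give loadings on the 6-month outcome; if the outcome helps choose the 25 predictors, the 10-per-predictor and over-fitting claims fail for cohort 1

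*Protocol article*

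**What the plan says.** The protocol article describes the data-reduction step in two places.

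- **Sample size:** "The number of predictors will be reduced using exploratory factor analysis". The outcome is not mentioned. This reduction is what is said to secure "at least 10 cases per candidate predictor".
- **Statistical analysis methods and management of missing data:** "Outcome (CPGS) scores will be dichotomised into good and poor categories as described previously", followed directly by "Data reduction will use exploratory factor analysis to assess factor loading of candidate predictors (summary scores) on poor outcome at 6 months". The aim is for the number of "candidate predictors entered into the final model to be reduced to 25, which can be supported by the cohort sample of 250". The same paragraph credits the step with lowering the risk of over-fitting and of picking wrong variables because predictors are correlated.

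The starting list is given under Candidate predictors: "Candidate predictors are summarised in table 1". After the reduction, the section on risk groups and the screening tool keeps items with P<0.05 in the logistic regression, plus items that experts want retained, and fits the final model to the first cohort. The section on development versus validation then assesses discrimination, calibration and goodness of fit in the second cohort. Table 2 promises that internal validation will be reported.

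**The concern.** Exploratory factor analysis models the correlations among the variables entered into it. A predictor has a loading on a latent factor. It has no loading on an observed outcome outside the factor model, so the sentence cannot be carried out as written. An analyst has to replace it with something else, and there are two candidates:

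- ordinary factor analysis of the baseline predictors, which ignores the outcome;
- some ranking or filtering of predictors by their relation to poor outcome.

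The two differ in their consequences. Reducing predictors without looking at the outcome spends no degrees of freedom on the predictor-outcome relation, so counting only the 25 survivors is fair. If the outcome decides which 25 survive, every candidate has been tested against it and every candidate belongs in the count. The sample-size argument and the over-fitting claim both depend on which analysis is meant. What is at stake is the identification of predictive factors (objective 1) and the development of the model (objective 2), because selection at P<0.05 follows in the same patients.

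**Working it through.** **1. The plan's own figure.** Inputs: 250 analysed per cohort and 10 cases per predictor. 250/10 = 25, so the stated limit of 25 reproduces.

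**2. Candidates before reduction.** Rows of Table 1 with a baseline tick: 11 general + 5 quality of life and function + 5 psychosocial + 6 injury + 5 pain + 4 sensory testing + 2 biomarkers = 38. The CPGS row has no baseline tick and is left out. Some rows hold more than one variable (nuclear and mitochondrial cell-free DNA; anxiety and depression; intensive care, ward and total days), so 38 is a minimum.

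**3. Ratio under each reading**, on the protocol's own basis of participants per predictor:

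- outcome not used: 250/25 = 10;
- outcome used to choose the 25: at most 250/38 = 6.6.

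**4. How much protection is lost.** This was simulated with 400 runs per setting, n = 250, and 38 candidates in seven blocks sized like the Table 1 domains. Three sets were compared: 25 chosen without the outcome (at random), the 25 most strongly correlated with the outcome, and all 38. Each was fitted by logistic regression and tested in a fresh cohort of 250. The prevalence of poor outcome (30% or 50%), the within-domain correlation (0 or 0.3) and the true effects are assumptions; the documents give none of them.

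Apparent AUC with no true effects (true AUC 0.50):

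| Prevalence | Correlation | Blind 25 | Outcome-chosen 25 | All 38 | Share of protection lost |
|---|---|---|---|---|---|
| 30% | 0 | 0.695 | 0.735 | 0.745 | 0.040/0.050 = 80% |
| 30% | 0.3 | 0.694 | 0.725 | 0.742 | 0.031/0.048 = 65% |
| 50% | 0 | 0.680 | 0.717 | 0.726 | 0.037/0.046 = 80% |
| 50% | 0.3 | 0.680 | 0.709 | 0.726 | 0.029/0.046 = 63% |

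The last column is (outcome-chosen minus blind) divided by (all 38 minus blind). Over the same settings, the share of the 25 retained noise predictors reaching P<0.05 rises from 5.7-6.3% (about 1.4-1.6 predictors) to 8.1-9.5% (about 2.0-2.4).

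**5. Second cohort.** With five true predictors (log-odds 0.4 per SD), AUC in the fresh cohort was 0.65-0.66 after outcome-based choice and 0.62-0.63 after random choice. Screening in cohort 1 therefore did not damage discrimination in cohort 2. Random choice is a crude stand-in for factor analysis, so all these sizes are illustrative.

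**The case against.** The strongest reply is that the sentence is loose wording for an ordinary factor analysis. The sample size section describes the step without the outcome, and one of the stated aims, dealing with correlation between predictors, needs no outcome. This stands as far as intention goes: the documents do not establish that the outcome will be used. They do not rule it out either. The outcome is dichotomised immediately beforehand and then named as what the predictors load on.

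A second reply is that the second cohort is independent and internal validation is promised. The first half stands in full, since selection and fitting use cohort 1 only. Internal validation would help, but the article does not say that the reduction would be repeated inside it. Such detail may sit in a fuller document.

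A reader might infer more than the text supports:

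- **That the plan certainly uses the outcome, or hides its use.** The first is unsettled. The second is wrong, because the outcome is named openly; what would be missing is its cost in the 10-per-predictor count.
- **That a factor analysis blind to the outcome must put factor scores in the model, against the wish that "it should be sufficiently brief to facilitate use in clinical practice".** Nothing in the article mentions factor scores. It speaks of predictors entering the model and plans to test whether single items can replace questionnaires.
- **That the ratio should be quoted per event.** The documents give no expected number of poor outcomes, and participants versus events is a separate question.

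**Conclusion.** The point holds. The statement about loadings on the outcome is wrong as a description of the method, whatever the figures, and the two sections describe the step differently. The rest is conditional. If the outcome helps choose the 25, the ratio is at most 6.6 participants per candidate instead of 10. Under the simulated null settings, 63-80% of the reduction in apparent over-fitting disappears: apparent AUC rises by about 0.03-0.04, and the share of noise predictors reaching P<0.05 goes from about 6% to 8-10%. The damage is moderate and confined to cohort 1: variable selection, P values, odds ratios and apparent performance. Performance estimated in the second cohort is not biased by it. If the reduction is blind to the outcome, only the wording is at fault and the 250/25 = 10 count stands on its own terms.

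**What to change.** In the statistical analysis section, delete the words that make the 6-month outcome the target of the loadings. State that data reduction uses baseline candidate predictors only, blind to the CPGS outcome, and that one representative measure per factor is carried forward, chosen without reference to the outcome. Bring the sample size section into line.

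If outcome-based screening is intended, call it that, count all Table 1 parameters in the cases-per-predictor figure, and repeat the screening inside the internal validation promised in Table 2.

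The cost is wording and minor programming, with no change to data collection. It should be settled before cohort 1 outcomes are analysed, because a blind reduction cannot credibly be claimed afterwards.

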**Methods and analysis:**

A prospective observational study will recruit two temporally staggered cohorts (n=250 each cohort; at least 10 cases per candidate predictor) of consecutive patients with acute musculoskeletal trauma aged ≥16 years, who are emergency admissions into a Major Trauma Centre in the United Kingdom, with an episode inception defined as the traumatic event. The first cohort will identify candidate predictors to develop a screening tool to predict development of chronic and disabling pain, and the second will allow evaluation of the predictive performance of the tool (validation). The outcome being predicted is an individual’s absolute risk of poor outcome measured at a 6-month follow-up using the Chronic Pain Grade Scale (poor outcome ≥grade II). Candidate predictors encompass the four primary mechanisms of pain: *nociceptive* (eg, injury location), *neuropathic* (eg, painDETECT), *inflammatory* (biomarkers) and *nociplastic* (eg, quantitative sensory testing). Concurrently, patient-reported outcome measures will assess general health and psychosocial factors (eg, pain self-efficacy). Risk of poor outcome will be calculated using multiple variable regression analysis.

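### The limit of 25 predictors for 250 participants counts participants, not outcome events: the planned logistic model has at most 5 events per predictor, and substantial overfitting is likely

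*Protocol article*

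**What the plan says.** The abstract (Methods and analysis) ties the cohort size to the rule: "n=250 each cohort; at least 10 cases per candidate predictor". The Sample size section says that exploratory factor analysis will reduce the number of predictors and adds: "This process will ensure that the sample size provides at least 10 cases per candidate predictor, to adequately power the final regression analysis". It plans for 300 recruits per cohort so that "final data are available for 250 participants per cohort (n=500 total").

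The section on statistical analysis methods and missing data fixes the number: predictors are to be "reduced to 25, which can be supported by the cohort sample of 250". The same section gives the model: "a logistic multivariable regression model will be fitted to the dichotomised outcome scores". Under Outcome, "poor outcome will be defined as grade ≥II" on the Chronic Pain Grade Scale. The section on risk groups and the screening tool says that the parameter estimates come from the first cohort only, with items chosen at P<0.05 or by expert opinion. No section gives an expected proportion with poor outcome or an expected number of events.

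**The concern.** In a binary logistic regression, information about the coefficients is limited by the smaller of the two outcome groups, not by the total number of participants. A limit of 10 per predictor computed on participants therefore allows at least twice as many predictors as the same limit computed on events.

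This matters because the study's product is an individual's absolute risk of poor outcome, meant to inform rehabilitation decisions. A model with too many candidates for its events gives coefficients that are too extreme and an apparent performance that is too good. In new patients the predicted risks are then spread too widely: high risks are overstated and low risks understated. The sample-size section assures the reader that this has been prevented.

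**Working it through.** **Inputs from the protocol.** Participants with final data in the development cohort: 250. Predictors entered: 25. Rule: at least 10 cases per candidate predictor. Outcome: binary. Development data: first cohort only.

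**Input not in the protocol.** The proportion f with poor outcome at 6 months. It is varied below.

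**Step 1: reproduce the stated figure.** 250/25 = 10. This matches, so a case is a participant.

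**Step 2: count the smaller outcome group.** Events per predictor = 250 × min(f, 1−f)/25. The largest number of predictors at 10 events each is 250 × min(f, 1−f)/10, rounded down. The development cohort needed to keep 25 predictors at 10 events each is 250/min(f, 1−f).

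| Split | Smaller group | Events per predictor (25) | Predictors allowed at 10 each | Cohort needed for 25 |
|---|---|---|---|---|
| 50/50 | 125 | 5.0 | 12 | 500 |
| 40/60 | 100 | 4.0 | 10 | 625 |
| 30/70 | 75 | 3.0 | 7 | 834 |
| 20/80 | 50 | 2.0 | 5 | 1250 |

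The ceiling of 5 needs no assumption, because min(f, 1−f) cannot exceed 0.5. If only poor outcomes are counted, whatever their frequency, 10 per predictor would need all 250 participants to have a poor outcome, and then no model can be fitted.

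**Step 3: expected shrinkage.** Solve S = 1 + P/(n·ln(1 − R²/S)), with n = 250 and R² taken as a share of its maximum, 1 − [f^f(1−f)^(1−f)]². Worked case: f = 0.5 gives a maximum of 0.75. A 15% share gives R² = 0.1125, and with P = 25 the solution is S = 0.56. Results over shares of 15–40% (assumed):

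- P = 25: f = 0.2, S = 0.51–0.76; f = 0.3, 0.54–0.78; f = 0.4, 0.55–0.79; f = 0.5, 0.56–0.79.
- P = 12: S = 0.68–0.88 over f = 0.2 to 0.5.

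All values lie below the usual target of 0.9, including those for 12 predictors.

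**Step 4: simulation.** Unpenalised logistic models were fitted with n = 250, 25 predictors, prevalence 30–50% and true C about 0.70–0.78 (all assumed). The median calibration slope in new patients was about 0.4–0.6 for the full model. After selection at P<0.05 and refitting it was about 0.5–0.7, with typically 2 to 3 predictors retained. The ideal slope is 1. Expert-retained items were not simulated.

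**The case against.** **The arithmetic is right.** 250/25 is 10, and the protocol says cases, not events. Read as participants, the ratio is true of the 25 predictors entered. This stands, and a reader should not infer a miscalculation. The defect is the unit: a participant ratio does not support the claim that a logistic model is adequately powered.

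**Overfitting is not certain.** A reader might infer that the model will be badly overfitted. The protocol does not establish that: it gives neither prevalence nor predictor strength, and it does not rule out shrinkage, which a fuller plan may specify. The quality table also commits to internal validation. What stands is that substantial overfitting is likely over the whole range examined. Shrinkage specified elsewhere would reduce it without making the stated justification correct.

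**The tool is not the full 25-predictor model.** Items are selected at P<0.05 or by expert opinion, and the model is then simplified. Selection does raise the simulated slope, so the full-model figures overstate miscalibration of the selected model. The slope still stays well below 0.9.

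**The rows of Table 1.** A reader might divide the events by every baseline row of Table 1 to get a still lower ratio. That is not supported. Factor analysis comes before the regression, and if it ignores the outcome, the original rows are not all candidates in the outcome model. The protocol's wording on factor loading leaves this unclear, but that is a separate question.

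**The second cohort would reveal miscalibration.** It would, before the tool is relied on. That limits the harm but does not prevent it.

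**Conclusion.** The point holds. With 250 participants and 25 predictors, the planned model has at most 5 outcome events per predictor, against the 10 cases on which its adequacy is claimed. It has fewer if the outcome split is uneven. This ceiling rests on the protocol's own numbers alone. On an events basis the limit of 25 is at least about twice what a rule of 10 allows.

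The size of the consequence is conditional. With assumed prevalence of 20–50% and R² at 15–40% of its maximum, expected shrinkage is about 0.5–0.8. Simulated slopes (prevalence 30–50%) are about 0.4–0.6 before selection and about 0.5–0.7 after it. These figures support saying that substantial overfitting is likely, and no more than that.

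**What to change.** - In the abstract, Sample size and statistical analysis sections, restate the ratio as at most 5 outcome events per predictor. Delete the statements that 10 per predictor is ensured and that 250 participants support 25 predictors.
- State an assumed prevalence of poor outcome. Set the number of candidate parameters in advance, either from the smaller outcome group (at most 12 for 250 participants at 10 per parameter, fewer if prevalence is away from 50%) or from a shrinkage-based calculation. Count parameters, so that a predictor entered as several categories or scores counts more than once.
- Because a limit of 12 alone does not reach a shrinkage of 0.9, also fit with penalisation, or apply bootstrap shrinkage that repeats the selection step in each resample.

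Cost: at least half of the 25 planned predictors would not enter the model under the events rule, the stated ratio becomes less favourable, and there is a little more analysis work. No extra patients are needed. Keeping 25 predictors at 10 events each would instead need at least 500 participants with final data in the development cohort.

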### Participants

Participants will be recruited from the register of a Major Trauma Centre in the United Kingdom for a period of up to 24 months (planned start date January 2018). All consecutive eligible patients will be approached for recruitment until the sample size is achieved.

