Gender	Female/male/other	√			
BMI	Calculated from height and weight measurements	√			
Education	Highest educational level attained	√			
Employment status	Full time/part time/not working/retired/student Employed/self-employed	√	√	√	√
Circumstance of trauma	Military/civilian	√			
Previous history of musculoskeletal pain and injury	Patient history data from patient recollection and medical records	√			
Comorbidity of other health problems	Patient history data from patient recollection and medical records	√			
Premorbid physical health	Patient history data from patient recollection and medical records	√			
Premorbid psychological health	Patient history data from medical records and patient recollection (including non-somatic items from the Subjective Health Complaints Inventory)^44^	√			
Number of days in hospital	Intensive care/ward/total	√			
Quality of life and physical functioning					
General health	SF-36v2^45^	√	√	√	√
Health-related quality of life	EuroQol EQ-5D-5L^46^	√	√	√	√
Self-care and mobility during activities of daily living	Barthel Index of Activities of Daily Living,^47^ collected from hospital data	√			
Sleep quality	11-point (0–10) Numerical Rating Scale, relating to current pain, from ‘best possible sleep’ to ‘worst possible sleep’^48^	√	√	√	√
Brain/CNS impairment	Glasgow Coma Scale^19^	√			
Psychosocial features					
Anxiety and depression	HADS^49^	√	√	√	√
Coping strategies applied during a painful experience	CSQ-24^50^	√	√	√	√
Fear of movement or fear of injury or re-injury during movement	TSK-11^51^	√	√	√	√
Confidence in ability to perform activities despite pain	Pain Self-Efficacy Questionnaire^52^	√	√	√	√
Subjective post-traumatic distress	IES-R^53^	√	√	√	√
Injury characteristics					
Time of injury/incident	Hospital record data	√			
Injury location	Adapted pain drawings, based on hospital record data	√			
Tissues damaged	Based on imaging data and hospital records Fractures Penetrating/non-penetrating injury/both	√			
Surgery required	Location and postinjury timing of surgery, based on hospital record data	√			
Assisted mechanical ventilation required	Yes/no/duration	√			
Severity of injury	Injury Severity Scale^54^	√			
Pain characteristics					
Chronic pain severity	Chronic Pain Grade Scale^21^			√	√
Pain intensity	11-point (0–10) Numerical Rating Scale, relating to current pain, from ‘no pain’ to ‘pain as bad as could be’ (collected as part of the Chronic Pain Grade Scale)	√*	√	√	√

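### Injury severity, a patient-level candidate predictor in a single-centre study, is named as a source of clustering; it should enter the model as an ordinary predictor

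*Protocol article*

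**What the plan says.** Under Statistical analysis methods and management of missing data, "a logistic multivariable regression model will be fitted to the dichotomised outcome scores". An odds ratio is promised for each candidate predictive factor, "adjusted for other factors and account for clustering (eg, level of injury severity"). Severity is the only example of clustering given, and no method is attached to it. The same section describes the modelling as planned in advance.

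Table 1 lists severity among the injury characteristics, measured at baseline by the "Injury Severity Scale". The Candidate predictors section confirms the status of that list: "Candidate predictors are summarised in table 1". On the sampling frame, the Participants section says "Participants will be recruited from the register of a Major Trauma Centre in the United Kingdom".

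The section on risk groups and the screening tool says "Items will be selected for the model if they are statistically significantly (P<0.05) associated with poor outcome in the logistic regression analysis", together with "those deemed clinically important to retain using expert opinion (regardless of statistical significance, study steering group"). The final model is then expressed through its alpha and beta terms and used to give an individual's absolute risk.

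**The concern.** A cluster is a sampled group, such as a hospital, whose members share influences that the model does not measure. Injury severity is a measured attribute of one patient. Two patients with similar scores do not thereby have correlated residuals once severity is in the model. Here there is one centre and no unit above the patient.

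The sentence lists adjustment for other factors and accounting for clustering as two separate things. An analyst who follows it literally would therefore do something with severity beyond entering it as a covariate. Two things are at stake:

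- **Item selection.** Items enter the tool on P<0.05, so a distorted standard error changes which predictors are kept.
- **Severity itself.** The Discussion names injury severity among the measures that stand for the nociceptive mechanism. If it is handled as a nuisance grouping, it may not contribute to the predicted risk as an ordinary predictor would.

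**Working it through.** **The plan's own figures.** 250 / 10 = 25 predictors, and 300 × (1 − 1/6) = 250 participants per cohort. Both reproduce, and neither depends on the clustering clause.

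**Inputs from the article.** n = 250 in the development cohort, up to 25 predictors, logistic regression, selection at P<0.05, one centre.

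**Assumed inputs.** Severity in G = 3, 4 or 5 bands, log-odds for severity 0.5 per SD, about 40% poor outcome, and a tested null predictor unrelated to severity. The article gives neither bands nor method.

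**Reading 1: cluster-robust variance with severity bands as clusters.** The middle of this variance is a sum of G score vectors multiplied by their transposes. The scores sum to zero at the estimate, so its rank is at most G − 1. That is 2 to 4, for 26 coefficients (25 plus intercept). The covariance matrix was rank-deficient in every simulated dataset in which this was checked. False-positive rates for one null predictor, with 600 to 1,500 datasets per setting and 5 to 25 predictors, were:

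| Bands | Robust, cut-off 1.96 | Robust, t on G − 1 df | Severity as fixed covariate, ordinary SE |
|---|---|---|---|
| 3 | 0.19–0.22 | 0.057–0.063 | 0.043–0.072 |
| 4 | 0.14–0.17 | 0.047–0.059 | 0.045–0.075 |
| 5 | 0.11–0.14 | 0.047–0.055 | 0.050–0.067 |

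The Monte Carlo standard error at a true 5% with 600 datasets is √(0.05 × 0.95 / 600) = 0.009. Individual runs in the second column span about 11–22%; about 13–21% is a fair summary from 5 bands to 3. If all 25 predictors were null, the expected number wrongly selected would be 25 × 0.05 = 1.25 at the nominal level, against 25 × 0.13 = 3.25 to 25 × 0.21 = 5.25.

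The t reference repairs the error rate by raising the cut-off from 1.96 to 4.30, 3.18 or 2.78 (2, 3 or 4 degrees of freedom). A real predictor with about 80% power under ordinary standard errors (log-odds about 0.4 per SD here) then has about 32% power with 3 bands, rising to about 57% with 5. A repeat of this calculation agreed.

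**Reading 2: random intercept or conditioning stratum.** This was reasoned through, not simulated. A conditional likelihood removes the stratum terms, so no severity coefficient is estimated. A random intercept gives severity a variance, estimated from very few levels, and no odds ratio. Either conflicts with the promise of an odds ratio for each candidate factor and with a tool built from alpha and beta terms. A random intercept need not make the other predictors' standard errors invalid.

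**Reading 3: fixed covariate or fixed strata.** The last column of the table applies. Error is close to nominal and severity keeps its own coefficient.

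**The case against.** The strongest reply is that this is loose wording and nothing more. The article names no robust variance, random effect or conditional likelihood, and severity appears only as an example. A condensed article may leave the method to a fuller document. The same sentence promises an odds ratio for each candidate factor, which on its plain words includes severity. The steering group may also keep clinically important items whatever their P value. The inflated error rate arises only with the 1.96 cut-off and disappears with a t reference. Banding is assumed, and Table 2 leans towards continuous variables.

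Much of this stands. A reader might infer that the clause makes the standard errors invalid, or that it removes severity from the tool. The article supports neither as a certainty, because the harmless fixed-covariate reading remains open and the steering group has a route to retain severity.

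Three things survive:

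- The point concerns what the article states. It names a patient-level predictor as a cluster, which is a misconception and not an omitted detail.
- The t reference exchanges false positives for a large loss of power, so clustering on a few severity bands harms P<0.05 selection either way. Retention by expert opinion cannot undo false positives among the other predictors.
- If a covariate was meant, the phrase about adjustment for other factors already covers it, and the clustering phrase still needs to go.

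It is also fair that some other grouping could exist. Data handling mentions three trained assessors. That is a reason to name the unit and method; it does not make severity a cluster.

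**Conclusion.** The point holds in conditional form. Injury severity is wrongly described as a source of clustering. If the clause is carried out as a cluster-robust variance on 3 to 5 bands, the chance of selecting a null predictor is about 13–21% with a normal reference. With a t reference the error is near nominal, but power falls from about 80% to about 32–57%. If it is carried out as a random intercept or conditioning stratum, severity loses the odds ratio and beta term that the article promises. If severity is simply a covariate, no harm follows and only the wording is wrong.

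The sizes rest on the assumed number of bands, outcome rate and effect sizes, none of which the article gives. The misclassification of severity rests on none of them. The sentence should be corrected before the development model is fitted.

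**What to change.** Replace the clustering clause with a statement that injury severity is entered as an ordinary fixed candidate predictor, preferably as a continuous score, with its odds ratio reported like the others and with model-based or bootstrap standard errors. Remove severity as a clustering unit. If the investigators have a genuine grouping in mind, name the unit and a method valid for the number of groups; otherwise drop the clustering adjustment.

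The cost is one sentence. No new data, patients or change to the sample size are needed.
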